**Methods:**

The study is designed as a single-center, single-blind, pilot, randomized, parallel-group study. After the screening, participants are randomly allocated to two groups, stratified by mechanical ventilation status. The intervention group will be provided with exercises of in-bed cycling/stepping according to the level of consciousness, motor power, and function in addition to conventional rehabilitation. In contrast, the control group will be provided with only conventional rehabilitation. The length of intervention is from ICU admission to discharge, and interventions will be conducted for 20 minutes, a maximum of three sessions per day.

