**Discussion:**

This study is a pilot clinical trial to investigate the feasibility and safety of conventional rehabilitation with additional in-bed cycling/stepping in critically ill patients. If the expected results are achieved in this study, the methods of ICU rehabilitation will be enriched.

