### Recruitment

Clinicians in the ICU at our hospital will collaborate to enroll patients for this clinical trial. Additionally, posters about this study are planned to be affixed on the noticeboard in front of the ICU, facilitating easy access to information regarding the clinical trial for representatives of patients. The principal investigator will provide a detailed explanation of the study to the participants’ legal representatives since most admitted patients are critically or severely ill. The study will not exclude patients who are likely to participate based on their socioeconomic status. This study is a pilot clinical trial to investigate the feasibility and safety of in-bed cycling/stepping exercise intervention and aims to recruit at least 24 participants. Assuming a 20% loss for death and a 15% loss for follow-up, the required sample size was 12 per arm to be recruited in this study.

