### Interventions

#### Conventional rehabilitation

Patients in the control group will only receive conventional rehabilitation in the ICU. The protocol for conventional rehabilitation in the ICU is shown in Fig 1. An standardized stepwise ICU rehabilitation program is provided for 20 min based on the stage of the patient’s condition, which is evaluated prior to each treatment session and considers consciousness, motor power, and functional mobility according to previous studies [10, 15]. The stage of the patient’s condition is graded as the 7-Likert scale from red (least able) to violet (most able) [21, 22], which means that the patient’s state of consciousness, muscle strength, and function improve sequentially. Generally, rehabilitation for critically ill patients is performed depending on the condition of critically ill patients [23, 24]. The goal of the conventional rehabilitation at each stage is lying without contractures, turning self, sitting balance, sitting at the edge, standing and transferring from bed to chair, assisted gait, and gait endurance. The conventional rehabilitation is provided by physiotherapists from ICU admission to hospital discharge, and the routine frequency of conventional rehabilitation is one session per day during weekdays.

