#### In-bed cycling/stepping

Patients in the intervention group will receive conventional rehabilitation plus exercise intervention with an in-bed cycle ergometer/stepper for additional 20 min in the ICU. The protocol, including exercise intervention, was developed by modifying the rainbow mobilization scales and the existing intensive care rehabilitation protocol shown in Fig 1. As the condition of the critically ill patient improves from yellow to violet, the intervention gradually progresses to passive, active assistive, active, and resistive exercise. In-bed cycling/stepping is provided by physiotherapists from ICU admission to discharge, and the routine frequency of in-bed cycling/stepping is 1–3 sessions per day on the weekdays during ICU hospitalization. The number of in-bed cycling/stepping interventions will gradually be increased depending on the patient’s condition [23]. Cycling is performed if there is one session per day; cycling-stepping if there are two sessions per day; and cycling-stepping-cycling if there are three sessions per day. During the intervention, the target rating of perceived exertion ranges from moderate to hard, and the exercise intensity is adjusted in this range [25, 26].

Risk criteria for delaying or terminating ICU rehabilitation will be assessed to determine patients’ suitability to participate in rehabilitation before and during rehabilitation sessions (Table 2) [15, 16]. ICU rehabilitation should be delayed or ceased if there is no recovery within two minutes under any of the conditions. Adverse events will be recorded after rehabilitation sessions. To improve intervention adherence, the participants are provided with an exercise log. Usual care, such as pulmonary rehabilitation and occupational therapy, will be maintained for all patients during the trial. Additionally, usual care will be maintained for all patients following trial completion.

**Table 2 pone.0301368.t002:** Criteria for delaying or terminating ICU rehabilitation and exercise intervention.

Respiratory conditions
ㆍPercutaneous oxygen saturation (SpO_2_) < 88% ㆍRespiratory rate (RR) > 40bpm ㆍUnsecure airway

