### Statistical methods

Statistical analysis in this study will be conducted using SPSS (version 25.0; IBM, Armonk, NY, USA). All statistical analyses will be performed for an intention to treat and a per protocol population. The outcomes of the continuous variables will be analyzed using Mann-Whitney U test, whereas the discontinuous variables will be analyzed using the chi-square test or Fisher’s exact test for variables between the two groups at the same time. Additionally, subgroup analysis will be conducted between the stratified groups Multiple imputation by chained equations algorithm will be used to handle missing data. The datasets analyzed and codes used for these analyses will be available from the corresponding author upon reasonable request.

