## Discussion

This is the study protocol to investigate the feasibility and safety of conventional rehabilitation with additional in-bed cycling/stepping in critically ill patients. Due to the dynamic nature of critical illness, the initiation and dosage of early rehabilitation may vary. To examine the feasibility and safety of the intervention, the outcomes of this study were as follows: the number and percentage of completed in-bed cycling/stepping sessions, the duration and percentage of in-bed cycling/stepping sessions, and the number of cessations of in-bed cycling/stepping sessions. Several previous clinical studies have reported that in-bed cycling is feasible in critical illness patients [9, 17, 30–32]. Patients received in-bed cycling with approximately 5–6 sessions, completing 79–90% of planned sessions on average in the ICU [17, 31, 33]. Additionally, in-bed cycling is safe and has a low rate of ceased sessions and adverse events in critically ill patients [9, 23, 31, 33, 34]. Detailed safety criteria and guidelines for delay or cease of the intervention may contribute to the safe implementation of the in-bed cycling/stepping intervention in the protocol of this study (S1 File).

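### The cycling/stepping feasibility outcomes exist only in the intervention arm, but the only analysis stated is a two-group test, which says nothing about feasibility

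*Protocol article*

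**What the plan says.** The Recruitment section gives the aim: "This study is a pilot clinical trial to investigate the feasibility and safety of in-bed cycling/stepping exercise intervention". The Discussion says how this will be examined: "the outcomes of this study were as follows: the number and percentage of completed in-bed cycling/stepping sessions", followed by the duration of those sessions and the number of times they were ceased. Table 3 adds the interval from ICU admission to the first cycling/stepping session.

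The arms differ in exactly this component. The Conventional rehabilitation section states: "Patients in the control group will only receive conventional rehabilitation in the ICU". The In-bed cycling/stepping section states: "Patients in the intervention group will receive conventional rehabilitation plus exercise intervention with an in-bed cycle ergometer/stepper". The abstract agrees that "the control group will be provided with only conventional rehabilitation".

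The Statistical methods section assigns continuous outcomes to the Mann-Whitney U test and discontinuous ones to the chi-square or Fisher's exact test, "for variables between the two groups at the same time". It adds intention-to-treat and per-protocol sets, a subgroup analysis by stratum, and multiple imputation by chained equations for missing data. It makes no separate provision for outcomes that exist in one arm. The abstract closes with: "If the expected results are achieved in this study, the methods of ICU rehabilitation will be enriched".

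**The concern.** A two-sample test needs a distribution in each arm. Controls have no cycling/stepping sessions to complete, to time or to cease, and no first session. Either their values are undefined and no test exists, or they are set to zero and the test asks whether patients given the device used it more than patients not given it. The answer to that question is known before the trial starts.

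The feasibility question is different: how much of the planned cycling/stepping was delivered, and how precisely is that known? The stated analysis does not address it. If the section is applied literally, the article could report a small p-value beside a session count and leave readers to take it as support for feasibility. The imputation sentence adds a second hazard: control cells left blank for these outcomes could be treated as missing and filled in, although they are not missing data.

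**Working it through.** **Inputs from the protocol.** 12 patients per arm (Recruitment); tests as listed in Statistical methods; roughly 5 to 6 sessions per patient in earlier in-bed cycling studies (Discussion).

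**Assumptions, not in the protocol.** Between-patient SD of percentage completed, 20 to 25 points; completion of 85% for the session-level illustration; within-patient correlation 0.3.

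The protocol gives no precision or target for these outcomes, so there is no figure of its own to reproduce.

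**1. Which outcomes are affected.** Counting each Table 3 entry once gives 28 outcomes. Four are cycling/stepping only: completed sessions, duration, cessations, and interval to first session. The other 28 − 4 = 24 can be measured in both arms, and two-group tests are a possible analysis for them.

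**2. What the test does if controls are scored zero.** Let k of 12 intervention patients have at least one session and 0 of 12 controls. The two-sided Fisher p-value is 2 × C(12,k) / C(24,k).
- k = 5: 2 × 792 / 42,504 = 0.037
- k = 6: 2 × 924 / 134,596 = 0.014

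So a pilot in which 7 of 12 patients never cycled would still fall below 0.05. If all 12 had at least one session, every intervention value would exceed every control value. The Mann-Whitney statistic would then be at its maximum whether patients completed one session or all of them, so the test cannot tell good delivery from poor.

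**3. What if controls are left blank.** There is one sample and no test. The interval to the first session can only be in this position, since zero would have no meaning for it.

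**4. What a one-arm estimate would deliver.** For mean per-patient completion, half-width = t(0.975, 11) × SD / √12, with t = 2.201.
- SD 20: 2.201 × 20 / 3.464 = 12.7 points
- SD 25: 2.201 × 25 / 3.464 = 15.9 points

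**5. Why the patient is the unit.** Pooling 12 × 5.5 = 66 sessions at 85% as if independent gives 1.96 × √(0.85 × 0.15 / 66) = 8.6 points. With correlation 0.3 the design effect is 1 + 4.5 × 0.3 = 2.35, and the half-width becomes 8.6 × √2.35 = 13.2 points. Ignoring clustering would overstate the precision.

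**6. Safety at the same sample size.** With no event in 12 patients, the one-sided 95% upper limit for the patient-level risk is 1 − 0.05^(1/12) = 22.1%.

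**7. The denominator.** The In-bed cycling/stepping section lets the number of daily sessions vary with the patient's condition, and the Fig 1 legend starts cycling/stepping at the yellow stage. A patient who never reaches that stage may have no planned session, so the percentage completed is 0/0. The choice matters. As a hypothetical case, suppose 9 of 12 patients become eligible and complete 90% on average. The result is 90% among the eligible, but 9 × 90 / 12 = 67.5% if the other three count as zero.

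**The case against.** The best defence is that the wording about variables between the two groups can be read as confining the tests to variables that have two groups. The cycling/stepping outcomes are themselves counts and percentages, which can simply be described. That is a fair reading, but it leaves the outcomes that carry the aim with no stated analysis, and the sentence itself makes no exception. The section needs correcting on either reading.

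It is also true that the two-group comparisons bear on the aim. Conventional sessions completed, their cessations, and adverse events exist in both arms and speak to safety and to displacement of usual rehabilitation. That stands, and the point is limited to the four cycling/stepping outcomes.

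A reader might go further in four ways that the protocol does not support.
- **That the pilot cannot conclude on feasibility at all.** Session counts can still be reported; what is missing is an analysis suited to them.
- **That the lack of a primary outcome or numerical target is an error.** A condensed article commonly leaves these to the full protocol or analysis plan, and the Discussion does single out three outcomes.
- **That the trial should adopt 79% as its criterion because earlier patients were** "completing 79–90% of planned sessions on average in the ICU". Those were studies of cycling, not of cycling plus stepping. A rule on the point estimate would also be missed about half the time if the true rate were 79%.
- **That chance findings across 28 tests are the main harm.** Only 24 outcomes can be compared, giving 24 × 0.05 = 1.2 expected false positives if every null held at a 5% level, which the protocol does not state.

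**Conclusion.** The point holds in a limited form. For completed cycling/stepping sessions, their duration, their cessations and the interval to the first session, the stated two-group tests are undefined or significant by design, and they carry no information on feasibility. The tests remain applicable to the outcomes measured in both arms.

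The consequence of a proper analysis is wide but honest intervals: about ±13 to ±16 points on mean completion with 12 patients, and a risk of up to 22% not excluded by zero events. The first range rests on an assumed SD of 20 to 25. It is also approximate near the ceiling: at 85% with SD 25 the upper limit is 85 + 15.9 = 100.9%, so a method that respects the 0 to 100 bounds would be better. The 22% and the Fisher results need only the 12 per arm.

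The abstract's reference to expected results is a secondary matter. It is a general closing sentence, not a decision rule, but a reader cannot tell what would count as achieving them.

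**What to change.** In Statistical methods:
1. Limit the Mann-Whitney, chi-square and Fisher tests to outcomes measured in both arms.
2. Estimate the cycling/stepping outcomes in the intervention arm only, with 95% confidence intervals at patient level, or by a method that allows for sessions clustered within patients.
3. Define the denominator of planned sessions, and say how patients who never become eligible to cycle are counted. If both versions are of interest, report completion among eligible patients and among all allocated patients.
4. State that controls are excluded from any imputation of these outcomes.

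Separately, the sponsor should say what the abstract's expected results are. The 79 to 90% from earlier cycling studies can serve as context and should not be imposed as a target.

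The cost is a few lines of analysis wording and a definition of planned sessions that the session records must support. The downside is that the wide intervals become visible.

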### Allocation

The computer-generated sequence will be generated on the website (https://mrcc.snuh.org) by an independent institution in our hospital. A computer-generated sequence will randomly allocate the two groups in this study. The stratified block randomization method will assign the randomization table to the control or intervention group at a 1:1 ratio. The use of mechanical ventilation will stratify the participants.

The group allocation will be performed by an independent researcher who is not involved in evaluating outcomes and will be concealed to physiotherapists who are engaged in assessing outcomes. The participants and in-bed cycling/stepping intervention provider will be instructed not to disclose the allocation to the evaluator. After the end of the clinical trial, blinding will be maintained until the input of evaluation data is completed. Any unblinding prior to clinical trials due to accidental or serious adverse events should be documented. To promote data quality for assessment and collection of outcomes, assessors will be well-trained.

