### Outcome measures

Baseline data will be measured prior to randomization, and follow-up data will be collected at ICU discharge, hospital discharge, and 1 and 3 months after hospital discharge. The following baseline clinical characteristics will be collected, shown in Table 3 [7, 23]: age, sex, weight, height, premorbid modified Barthel index, premorbid FAC, Acute Physiology and Chronic Health Evaluation (APACHE II) score [27], whether cardiopulmonary resuscitation (CPR) was performed within 24 hours before admission to the ICU, primary diagnostic category of ICU admission, and comorbidity, rehabilitation services after hospital discharge.

**Table 3 pone.0301368.t003:** Clinical examination items.

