The outcomes listed in Table 3 are the number and percentage of completed in-bed cycling/stepping sessions, the duration and percentage of in-bed cycling/stepping sessions, and the number of cessations of in-bed cycling/stepping sessions, the interval from ICU admission to the first session of in-bed cycling/stepping, the number and percentage of completed conventional rehabilitation sessions, the duration and percentage of conventional rehabilitation sessions, the number of cessations of conventional rehabilitation sessions, the number of adverse events, the confusion assessment method for the ICU (CAM-ICU), Richmond agitation-sedation scale (RASS), de Morton mobility index (DEMMI), FAC, functional status score for the ICU (FSS-ICU), short physical performance battery score (SPPB), falls efficacy scale (FES), activities-specific balance confidence scale (ABC), sum of Medical Research Council (MRC) score, handgrip strength, modified Barthel index, 36-item short-form survey (SF-36) version 2.0, days to initiate ambulation (FAC ≥2), mortality-28 days, duration of mechanical ventilation, length of stay in the ICU, length of stay in the hospital, Pittsburgh rehabilitation participation scale (PRPS), concomitant occupational therapy and its application dose, concomitant pulmonary rehabilitation and its application dose.

The schedule of enrollment and assessment of the participants are shown in Fig 2. After ICU admission, patients are screened according to the inclusion criteria. After the screening, the guardians of patients who meet the inclusion criteria will be given an information sheet and asked to provide written consent to participate in the trial. Patients will be enrolled in the trial, given a trial-specific identification number, and randomly allocated to a group using a computer-generated random sequence that is listed prior to the start of the trial. After baseline evaluation, patients will be assessed at ICU discharge, hospital discharge, 1 month after hospital discharge, and 3 months after hospital discharge. Measurements 1 month after hospital discharge will be conducted by a visit and measurements 3 months after hospital discharge will be performed over the phone.

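### Multiple imputation is prescribed for missing data with no exception for death, so as written functional and quality-of-life scores that do not exist after death would be imputed from survivors

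*Protocol article*

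**What the plan says.** All references are to the protocol article; no separate analysis plan is shown.

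- **Statistical methods, missing data:** "Multiple imputation by chained equations algorithm will be used to handle missing data". No outcome, cause of missingness or exception is named.
- **Statistical methods, populations and test:** "All statistical analyses will be performed for an intention to treat and a per protocol population". For continuous outcomes, "The outcomes of the continuous variables will be analyzed using Mann-Whitney U test". Discontinuous outcomes are compared by chi-square or Fisher's exact test.
- **Recruitment:** the trial "aims to recruit at least 24 participants", and "Assuming a 20% loss for death and a 15% loss for follow-up, the required sample size was 12 per arm". Death is thus budgeted as a loss, separately from loss to follow-up.
- **Outcome measures:** "follow-up data will be collected at ICU discharge, hospital discharge, and 1 and 3 months after hospital discharge". The outcomes include mobility scales, the MRC sum score, grip strength, the modified Barthel index and SF-36.
- **Outcome measures, including Table 3:** mortality is an outcome of its own, in the list that reads "days to initiate ambulation (FAC ≥2), mortality-28 days, duration of mechanical ventilation". No mortality outcome beyond day 28 appears.

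Nothing in the article separates a value that was not observed from one that cannot exist because the patient has died. Nor does it say how a living patient who cannot perform a test is scored.

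**The concern.** A survivor who misses a visit has a true score that nobody recorded, and imputation tries to recover it. A patient who has died has no grip strength or SF-36 score to recover. Chained-equation imputation would fill the gap from relationships seen in survivors, so the patient enters the intention-to-treat comparison with a survivor-like score.

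This matters here for two reasons. Death is the largest cause of missing follow-up that the plan itself expects, and safety is one of its two stated aims. If deaths differ between arms, the functional and quality-of-life comparisons would not show it. They would still be presented as results in all randomised patients, when they really answer how patients would have functioned had nobody died.

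**Working it through.** **1. The plan's own figure.** The article gives 12 per arm after allowing for 20% death and 15% loss, but no evaluable number before inflation, so 12 can only be solved backwards. An assumed base of 8 per arm gives 8 / (0.80 × 0.85) = 8 / 0.68 = 11.76, rounded up to 12, if the losses act in sequence. It gives 8 / 0.65 = 12.3, rounded up to 13, if they add. The point does not depend on this base.

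**2. How much missing follow-up is death.** Inputs from Recruitment: n = 24, death 20%, loss to follow-up 15%.

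- Expected deaths: 24 × 0.20 = 4.8. With allocation to the "control or intervention group at a 1:1 ratio" that is 2.4 per arm at equal mortality.
- Lost to follow-up, additive: 24 × 0.15 = 3.6. Share due to death: 4.8 / (4.8 + 3.6) = 57%.
- Lost to follow-up, sequential: 24 × 0.80 × 0.15 = 2.88. Share due to death: 4.8 / (4.8 + 2.88) = 62.5%.

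On either reading, more than half of the expected missing follow-up comes from death.

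**3. What imputing the dead does to a functional comparison.** The measure is the probability that an intervention patient scores higher than a control patient, counting ties as half. This is the quantity behind the Mann-Whitney test. Assume survivors' scores have the same distribution in both arms. With survival s_T (intervention) and s_C (control), ranking death worst gives

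s_T·s_C/2 + s_T(1 − s_C) + (1 − s_T)(1 − s_C)/2 = 0.5 + (s_T − s_C)/2.

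For mortality of 30% intervention and 10% control: 0.7 × 0.9 × 0.5 + 0.7 × 0.1 + 0.3 × 0.1 × 0.5 = 0.315 + 0.070 + 0.015 = 0.40.

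A simulation agrees. It used 12 per arm, 2,000 runs, survivors' scores with assumed mean 60 and SD 20, and 5 imputations drawn within arm from survivors.

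| Assumed mortality, control vs intervention | Dead imputed | Death ranked worst |
|---|---|---|
| 20% vs 20% | 0.50 | 0.50 |
| 30% vs 10% | 0.50 | 0.60 |
| 10% vs 30% | 0.50 | 0.40 |
| 40% vs 0% | 0.50 | 0.70 |

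The imputed comparison stays at 0.50 whatever the mortality split. A survivors-only comparison would also give 0.50 in every row, because survivors were assumed identical. The table therefore shows what the imputed analysis leaves out. It does not show a bias peculiar to imputation. The mortality splits and the score distribution are assumptions, not figures from the article.

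**4. What the separate mortality comparison can show.** The article states no significance level, so two-sided 5% is assumed. For 30% versus 10% with 12 per arm, the mean proportion is 0.20.

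- Null standard error: √(2 × 0.20 × 0.80 / 12) = 0.163.
- Alternative standard error: √((0.30 × 0.70 + 0.10 × 0.90) / 12) = 0.158.
- (0.20 − 1.96 × 0.163) / 0.158 = −0.76, which gives a power of about 22%.

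If five patients die in all, Fisher's exact test gives p = 1.00 for a 3–2 split, 0.32 for 4–1 and 0.037 for 5–0. Only the most extreme split reaches 5%.

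**The case against.** **The wording does not mention death.** The article never says that values after death count as missing data. Budgeting for death in the sample size fits equally well with dead patients leaving the evaluable set, and an analysis plan not shown may restrict the rule. This stands as a limit on certainty: imputing the dead is the natural reading of an unqualified sentence, not an express statement. It does not remove the point. The article did not leave missing data open; it committed to a method for an intention-to-treat population, and that method does not suit the largest expected cause of missingness.

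**Mortality is reported anyway.** A reader might infer that the rule hides every mortality difference. It does not: 28-day mortality is listed and would be compared between arms, and the Adverse events section sets data and safety monitoring after every five registrations. What stands is narrower. The functional and quality-of-life comparisons are blind to deaths, the 28-day test is weak, and deaths after day 28 have no listed outcome.

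**Stronger readings that the article does not support.**

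- *The imputation model has more variables than patients.* No model is described and the schedule figure is not shown, so its size is unknown.
- *Mann-Whitney results cannot be pooled over imputations.* The U statistic divided by the product of the arm sizes estimates a win probability, which can be pooled with its standard error. The article prescribes no pooling rule that would prevent this.
- *Sedated or weak patients will receive imputed scores.* The article does not say whether they are scored at the floor or left missing. This is a gap, not a stated error.
- *The arm with more deaths would look better.* The calculation shows only that the arms would look equal.

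**The trial is a pilot.** The Discussion ties the feasibility and safety aim to session completion, duration and cessations. These outcomes are largely unaffected, which lowers the severity.

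**Conclusion.** The point holds in a limited form. Followed as written, the rule would give about 5 of 24 patients functional, strength, daily-living and SF-36 scores after death, modelled on survivors. Those comparisons would then answer a question about a population without deaths. In the illustration they showed no difference (0.50) even at assumed mortality of 40% versus 0%, where ranking death worst gave 0.70.

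The count of 4.8 deaths and the 57% to 62.5% share rest on the plan's own rates. The between-arm contrasts rest on assumed mortality splits, identical survivors and a simple within-arm imputation model. A model using prior severity could shift the imputed scores, but they would still be scores for patients who have none.

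Severity is moderate: a stated rule needs its scope corrected, but the trial's feasibility conclusions do not depend on it.

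**What to change.** Amend Statistical methods as follows.

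1. Limit multiple imputation to values unobserved in patients known to be alive at that visit, and do not impute after death.
2. State how death enters each functional and quality-of-life comparison. Two approaches are reasonable: a composite in which death ranks below the worst survivor score, with the components shown; or survivor results shown beside the number of deaths by arm at each visit. Choose one before the data are seen.
3. State how a patient who is alive but cannot perform a test is scored.
4. Record and report vital status by arm at hospital discharge and at 1 and 3 months after it, because day-28 mortality does not cover this follow-up.

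The cost is a few sentences plus vital status at contacts already scheduled; no extra patients or visits are needed. The downside is small: the result becomes either a composite of survival and function or a result conditional on survival, and must be labelled as such.
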